## Statistical Analysis

The original assumptions for the statistical power calculations for this study were derived from a preliminary study by [name] et al. [18]. Based on recent studies, with ASAP gaining ground as a separate diagnosis, one-year progression rates for exclusive HGPIN range from 4.5% to 27%, centering around 20%. Meanwhile one-year progression rate estimates to prostate cancer for men with ASAP range from 25% to 59%, centering around 40%. Since we anticipate a 50-50 mixture of these two diagnoses, the estimated overall one-year progression rate for this study is 30%. To be conservative, the sample size is chosen to achieve 80% power if the treatment reduces the rate of prostate cancer within one year from 30% to 15%, a 15% reduction compared to the 27% decrease (from 30% to 3%) observed by [name] et al. [18]. The use of blocked randomization with diagnosis being one of two strata will ensure a balance of diagnoses in the two study arms. The analysis will be done overall using a single 2×2 unconditional test.

We plan to perform an interim analysis of the primary endpoint. The α level for the interim look will be .0125, leaving α = .041 for the final analysis. For an unconditional test at the two-sided 0.041 significance level, this requires 123 per group, for a total of 246. The interim look will be made when the first third of the patients (40 per group) has been on study for one year, which is when the primary endpoint is resolved for these patients. This is expected to occur at about the half-way time point in the study. The power for early termination will be 19% if the true cancer rates are 30% and 15%. If the true cancer rates are the same as the sample estimates from the Bettuzzi study, though, the power of early termination will be 85%. Thus, this interim analysis helps to guard against large but conceivable differences in cancer rates between the treatment arms.

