In order to achieve 240 evaluable subjects, we will accrue a total of 272 subjects, which allows for an estimated dropout rate of 10% during the run-in phase prior to randomization. This will provide us with 80% power for rates of 30% vs. 15% and 98% power if those rates are 30% and 10%. We also have 87% power for rates of 25% vs. 10%, and 85% power for rates of 20% vs. 7% and 85% power for rates of 15% vs. 4%. With the current sample size, the study will have greater power to detect a 15% difference even where the control group rates will be lower than 30%. In order to assess the effect of treatment on the extent of prostate cancer in those subjects who do develop prostate cancer while on study, we will use the following Gleason grade categories: 0 (for all subjects not diagnosed with prostate cancer), 1–6, 7–8, 9–10, and apply a Tukey trend test at α = .05 to the 2×4 contingency table.

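### The powers listed for 240 evaluable men are about 0.5 to 3 points higher than 120 per arm delivers at the plan's final α of 0.041

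*Protocol article*

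**What the plan says.** All the relevant text is in the Statistical Analysis section of the protocol article.

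- Test: "The analysis will be done overall using a single 2×2 unconditional test". The version of unconditional test is not named.
- Split of α: "The α level for the interim look will be .0125, leaving α = .041 for the final analysis".
- Sample size for 80% power at 30% vs 15%: "For an unconditional test at the two-sided 0.041 significance level, this requires 123 per group, for a total of 246".
- Interim timing: "The interim look will be made when the first third of the patients (40 per group) has been on study for one year".
- Interim power: "The power for early termination will be 19% if the true cancer rates are 30% and 15" (per cent). At the 30% and 3% seen in the earlier study, "the power of early termination will be 85" per cent.

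The next paragraph sets a target of 240 evaluable men from 272 accrued, allowing 10% loss in the run-in. It attributes to that number 80% power at 30% vs 15% and 98% at 30% vs 10%. It continues: "We also have 87% power for rates of 25% vs. 10%, and 85% power for rates of 20% vs. 7" (per cent), and closes with 85% for 15% vs 4%. No α stands beside this list. The only α of 0.05 in the section belongs to the Gleason trend test.

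**The concern.** Two adjacent paragraphs give the same 80% power at the same rates, one for 123 per group and the other for 120. If 0.041 needs 123 per group, 120 per group at 0.041 should fall short of 80%. The other four powers rest on the same 240 men, so they should be checked with it.

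The list is also the plan's evidence that the trial stays well powered if the control rate turns out to be 15% to 25% rather than 30%. A reader relying on it should be able to tell which n, which α and which test it describes, and the figures should hold for the n printed beside them.

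**Working it through.** **Inputs** (all from the Statistical Analysis section): two-sided α of 0.0125 at 40 per group and 0.041 at the end; 123 per group (246) or 120 per group (240); rate pairs 30/15, 30/10, 25/10, 20/7 and 15/4.

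**Test.** With x₁ and x₂ cancers among n men per arm and p̄ = (x₁ + x₂)/(2n), the pooled statistic is Z = (x₁/n − x₂/n) / √(2p̄(1 − p̄)/n). The article does not say which unconditional test is meant, so two versions were run:

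- Pooled Z: reject if |Z| reaches the normal critical value (2.498 at 0.0125, 2.044 at 0.041, 1.960 at 0.05).
- Size-controlled: same ordering, with the cut-off raised until the largest type I error over all common rates is at most α.

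**Power.** For one test, sum the product of the two binomial probabilities over all (x₁, x₂) in the rejection region. For both looks, power = P(reject at 40 per arm) + P(no rejection at 40 per arm, rejection at n per arm). The second term is found by convolving the first 40 per arm with the remaining n − 40.

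**Step 1: reproduce the plan's own figures.** Pooled Z at 40 per arm and 0.0125 gives 18.5% (stated 19%) for 30/15 and 85.3% (stated 85%) for 30/3. With both looks and 123 per arm it gives 79.8% for 30/15 (stated 80%). The size-controlled version gives 17.6% at the interim and 79.0% with both looks at 123 per arm. Pooled Z therefore fits these figures better.

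**Step 2: the list at the stated n of 120 per arm and α = 0.041 (power, %).**

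| Rates | Stated | Pooled Z, final test only | Pooled Z, both looks | Size-controlled, final test only | Size-controlled, both looks |
|---|---|---|---|---|---|
| 30/15 | 80 | 78.2 | 78.7 | 77.2 | 77.8 |
| 30/10 | 98 | 97.5 | 97.5 | 97.4 | 97.4 |
| 25/10 | 87 | 85.8 | 86.2 | 85.5 | 85.9 |
| 20/7 | 85 | 83.8 | 84.2 | 83.0 | 83.4 |
| 15/4 | 85 | 84.2 | 84.5 | 82.4 | 82.8 |

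Shortfall with both looks, in list order: pooled Z 1.3, 0.5, 0.8, 0.8 and 0.5 points; size-controlled 2.2, 0.6, 1.1, 1.6 and 2.2 points. The largest shortfall in the table is 80 − 77.2 = 2.8 points. The 98% for 30/10 is within about half a point of every column. The other four stated figures are missed in every column.

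**Step 3: what the list does fit (power, %).**

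| Rates | Stated | 123 per arm, 0.0125 then 0.041, pooled Z, both looks | 120 per arm, single α = 0.05, size-controlled |
|---|---|---|---|
| 30/15 | 80 | 79.8 | 79.8 |
| 30/10 | 98 | 97.9 | 97.8 |
| 25/10 | 87 | 87.2 | 87.3 |
| 20/7 | 85 | 85.2 | 85.3 |
| 15/4 | 85 | 85.4 | 85.5 |

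The first column rounds to the whole list. The second does so too, apart from 15/4, which sits on the edge between 85 and 86.

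**The case against.** The strongest defence is that the list contains no error of α. Taken as designed, with 0.0125 at 40 per arm and 0.041 at 123 per arm, pooled Z returns all five stated powers after rounding, and it also agrees with the two stated interim powers. The size-controlled version, which produces the larger shortfalls, first reaches 80% for 30/15 at 127 per arm, not 123, so it is probably not what the authors ran. On this view only a headcount mismatch of six men remains, worth 0.4 to 1.3 points of power, and no sample size, test or decision depends on it.

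Most of this stands. It does not rescue the text, because the list is tied to 240 evaluable men, and at 120 per arm even pooled Z with both looks falls below it.

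A reader might infer more, and the documents do not support it:

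- *That the list was computed at α = 0.05 and the cost of the interim look forgotten.* One version of the test fits that reading, but another fits the plan's own α levels at 123 per arm. The article never gives 0.05 for the primary test.
- *That this is a separate error from 240 versus 246.* If the list was computed for 123 per arm, the two are the same error.
- *That the overstatement is worst at the lowest control rate.* With pooled Z and both looks, the 15/4 gap is about 0.5 points, among the smallest. For the final test alone, 30/15 has the largest gap under either version.
- *That power for 15/4 is as low as 81%.* That figure comes from the pooled normal approximation, which would need 128 per group rather than the plan's 123, so it is not the plan's method. Enumeration gives 82.4 to 84.5%.

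**Conclusion.** The point holds in a limited form. With 120 per arm and a final two-sided α of 0.041, an unconditional 2×2 test does not deliver the listed powers. Counting both looks, they are about 78–79, 97–98, 86, 83–84 and 83–85%. Across both test versions, and with or without the interim look, the list is about 0.5 to 3 points too favourable.

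This assumes equal arms, 240 men evaluable at the final analysis, and either pooled Z or its size-controlled form as the unconditional test. The cause cannot be settled from the article. Severity is low: the design case stays close to 80%, and no design decision changes.

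**What to change.** Beside the list, state the n per arm, the α (final test at 0.041 alone, or both looks at 0.0125 and 0.041) and the version of the unconditional test. Recompute all five powers for that choice, including the 30% vs 15% design case. Then reconcile the two paragraphs in one of two ways:

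- If 240 evaluable men is the target, report the lower figures from the 120-per-arm table and drop the 80% claim for that number.
- If the list belongs to 246 men, say so and correct the evaluable target. The accrual figure should then be checked as well: 272 × 0.9 = 244.8, whereas 246 / 0.9 = 273.3, so 274 would be needed at the stated 10% loss.

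The first option costs wording only, with slightly less favourable powers. The second changes the evaluable target and, if the 10% allowance is kept, adds two men to accrual.

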## Secondary Study Objectives

The primary objectives of this study are to evaluate the effectiveness and safety of Polyphenon E (200 mg EGCG BID) (vs. placebo) administered for 1 year to men, following the diagnosis of HGPIN and/or ASAP. The primary efficacy endpoint is the progression to prostate cancer at one year. Men will be examined at three (ASAP) and six months (both) for a rise in PSA, as defined by a re-confirmed PSA increase of >0.75ng/ml or the development of a prostate nodule, and biopsied at 3 or 6 months if a rise in PSA or a nodule is detected, or after 12 months and the frequency of HGPIN, ASAP and CaP defined. If prostate cancer develops during the course of investigation, we will compare the extent and grade of the cancer following treatment. The primary safety endpoint is the incidence and severity of AE's during intervention evaluated using standard assessment of toxicity (ver. CTCAE 3.0) [37] based upon detailed questionnaires, including symptoms, clinical evaluation, and assessment of biological samples (comprehensive metabolic panel (CMP), complete blood count (CBC) and LFTs (SGOT/SGPT) completed by Quest Diagnostic laboratories throughout the study. Compliance to intervention is monitored using pill counts and agent logs, quarterly diet diaries and plasma catechins using HPLC-EC at baseline, 6 and 12 months. The effect of treatment with Polyphenon E on lower urinary tract symptoms using the Lower Urinary Tract symptoms Scale [38] and quality of life (QOL) using Rand Short-form (SF)-36 [39] is also evaluated.

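### The Gleason trend test is introduced as a question about men who develop cancer, but it is run on all men, so a significant result cannot be read as an effect on grade or extent among cancers

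*Protocol article*

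**What the plan says.** The objective is in the section headed Secondary Study Objectives of the protocol article: "If prostate cancer develops during the course of investigation, we will compare the extent and grade of the cancer following treatment". The same section fixes the primary outcome: "The primary efficacy endpoint is the progression to prostate cancer at one year".

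The last sentence of the Statistical Analysis section turns the objective into an analysis. Its stated purpose is to "assess the effect of treatment on the extent of prostate cancer in those subjects who do develop prostate cancer while on study". The categories are "0 (for all subjects not diagnosed with prostate cancer), 1–6, 7–8, 9–10", and the plan is to "apply a Tukey trend test at α = .05 to the 2×4 contingency table".

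The article describes no analysis restricted to men with cancer, and it names no measure of extent apart from Gleason grade.

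**The concern.** The purpose and the test sit in one sentence but refer to different populations. The purpose concerns men who develop cancer; the table contains every man. Most men fall in category 0, so the contrast between category 0 and the rest, which is the primary endpoint, carries much of the trend.

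This matters for how the result will be reported. If the drug lowers incidence and leaves grade among cancers unchanged, the test will usually be significant. Taken under its stated purpose, that result would be reported as an effect on the cancers themselves. A shift towards higher grade among the treated cancers could also go unseen behind a favourable p-value. The trial is meant to inform a phase III design (Future Directions), so the distinction has a use.

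An unseen analysis plan does not resolve this, because the article itself fixes the categories, the test and its significance level.

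**Working it through.** **Inputs from the article (Statistical Analysis).** Cancer rates 30% and 15%; 240 evaluable men, so 120 per arm; trend test at 0.05; primary test at two-sided 0.041 with 123 per group for 80% power.

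**Assumed inputs.** The article gives neither the Gleason mix among cancers nor the score sets. Mixes are written below as percentages in 1–6 / 7–8 / 9–10. Scores are 0,1,2,3; Gleason-type scores (0,6,8,10 or 0,6,7.5,9.5); and midranks.

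**The plan's own figure.** With unpooled variance, n = (2.044 + 0.842)² × (0.30×0.70 + 0.15×0.85) / 0.15² = 124.9, so 125 against the stated 123. An exact unconditional test has 78.5% power at 123 per group. The stated size is reproduced closely, so the design rates are a sound base for the expected counts.

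**Expected counts.** Cancers: 120 × 0.30 = 36 on placebo and 120 × 0.15 = 18 on drug. Category 0: 84 of 120 (70%) and 102 of 120 (85%).

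**Why incidence carries the trend.** With fixed scores and 0 for no cancer, the mean score in an arm is p × m, where p is the cancer rate and m the mean score among cancers. If m is the same in both arms, the expected difference is (0.30 − 0.15) × m, which is the incidence difference times a constant.

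- Scores 0–3, mix 75/20/5: m = 0.75 + 0.40 + 0.15 = 1.30, so the difference is 0.195. The mean squared score among cancers is 0.75 + 0.80 + 0.45 = 2.00. Variances are 0.30×2.00 − 0.39² = 0.448 and 0.15×2.00 − 0.195² = 0.262. The standard error is √(0.710/120) = 0.0769, so z = 2.54 and power is Φ(2.54 − 1.96) ≈ 72%.
- Scores 0,6,8,10, same mix: m = 4.5 + 1.6 + 0.5 = 6.6, so the difference is 0.99. The mean squared score is 27 + 12.8 + 5 = 44.8. Variances are 13.44 − 1.98² = 9.52 and 6.72 − 0.99² = 5.74. The standard error is √(15.26/120) = 0.357, so z = 2.78 and power is about 79%.
- Plain incidence: 0.15 / √(0.3375/120) = 2.83, so power is about 81%.

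**Simulation (120 per arm, two-sided 0.05, share of trials significant in favour of the drug).**

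| Scenario | 2×4 trend, by score set | Plain incidence test |
|---|---|---|
| 30% vs 15%, mix 75/20/5 in both arms | 72–80% | about 80–81% |
| 30% vs 15%, mix 50/40/10 in both arms | 72–80% | about 80–81% |
| 30% vs 15%, mix 85/13/2 in both arms | 74–80% | about 80–81% |
| 30% vs 15%, Gleason ≥7 at 7.5% of men in both arms (25% of placebo cancers, 50% of drug cancers) | 44–73% | about 80% |
| 30% vs 15%, Gleason ≥7 at 7.5% of men on placebo and 9% on drug | 33–70% | about 80–81% |
| 30% in both arms, drug mix 90/9/1 against 70/25/5 | 5–13% | 2.5% |

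In the first two rows the trend z correlates 0.90 to 0.99 with the incidence z. A Tukey-type test that takes the maximum over three score sets, with a simulated critical value, rejects in 78% of trials with mix 70/25/5 in both arms.

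**A comparison in cancers only.** With 36 against 18 expected cancers and no grade difference, a 2×3 trend test rejects in about 5% of trials, as it should. In the last scenario of the table (36 cancers per arm) it rejects in 57%.

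**The case against.** The best defence is that category 0 is a sound choice. Keeping every man in the table preserves the randomised comparison. A test in cancers only conditions on an event after randomisation and rests on some 54 cancers. The article defines the table openly, and a combined incidence-and-severity test that favours the drug when total cancers halve is doing its job. All of this stands. A reader might infer that the test is invalid or should be dropped; the documents do not support that.

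A reader might also infer that the test is nothing more than the primary endpoint again. That goes too far. With scores 0–3 it does respond to grade: support for the drug falls from 72% to 44% and then 33% as grade on drug worsens, while the incidence test stays near 80%. Gleason-type scores and midranks respond less. The score sets may be given in the full protocol or analysis plan.

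It is tempting, too, to offer the proportion of all randomised men with Gleason ≥7 cancer as the answer to the stated aim. It is not one, because it also counts cancer-free men. With mix 75/20/5 in both arms it falls from 0.30 × 25% = 7.5% to 0.15 × 25% = 3.75% through incidence alone.

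Finally, no passage says that a significant trend will be declared an effect on grade. That reading follows from the stated purpose and not from a decision rule. A measure of extent may also exist in the full protocol, so its absence from the article is not itself a fault. What remains is that the article's analysis sentence speaks of extent and uses grade.

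**Conclusion.** The point holds as a mismatch between the stated purpose and the specified test. The 2×4 test is a valid randomised comparison of incidence and grade combined. Under the design rates, with no grade difference among cancers, it favours the drug in about 72 to 80% of trials, so significance says little about grade among cancers. It has little ability to show a grade effect when incidence is equal: 5 to 13% in the case examined.

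The percentages rest on assumed grade mixes and score sets. The result with no grade difference barely moved across the mixes tried, and the algebra shows why: with a common mix and fixed scores, the expected difference is proportional to the incidence difference. The primary endpoint, its test, its significance level and the sample size are not affected. The fault touches a secondary conclusion and should be corrected.

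**What to change.** 1. In the Statistical Analysis section, describe the 2×4 trend test as a combined incidence-and-severity comparison in all men, and state that no conclusion about grade or extent among cancers will be drawn from it.
2. For the stated aim, tabulate Gleason category among men with cancer by arm, as description. State that these men are selected by an event after randomisation and that precision is low with about 36 and 18 expected.
3. If wanted, add the proportion of all randomised men with Gleason ≥7 cancer by arm, labelled as a randomised comparison of high-grade incidence and not as an answer about grade among cancers.
4. Replace the word extent by grade in that sentence, unless a measure of extent is specified.

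The cost is a change of wording and one or two tables. The grade tables need no new patients, visits or data.

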## Data Management and Study Monitoring

All collected data is entered from source documents or case report forms (CRF's) directly into the web-based ONCORE system by authorized, trained staff. Toxicities are monitored continuously through the trial by the PI and study physician at each site. Additionally, the study team is guided by an External Data and Safety Monitoring Board (EDSMB). Statistical analyses were performed and reviewed by the EDSMB when fifty patients completed at least one month on study and are repeated every six months (and more often if needed). The EDSMB can recommend early termination if a serious imbalance occurs and the estimated risk of harm appeared to warrant such action. Additionally, the study is monitored following a monitoring plan developed by the Protocol Review and Monitoring System at Moffitt Cancer Center.

## Future Directions

Poly E in HGPIN and ASAP is a Phase II, Randomized, Double-blind, Multi-centered Study, are ongoing at several clinical sites across the United States. The goal of this study is to evaluate the efficacy and safety of a promising chemopreventive agent (Polyphenon E) in a high risk population (men with HGPIN and/or ASAP) to inform the design of a larger Phase III clinical trial. Demonstration of efficacy and safety of Polyphenon E will be an important outcome, even if the mechanism(s) involved is not identified in this study, or is shown to be different from the one proposed. With baseline and post intervention specimens available including tissue from biopsy, serum, buffy coat and urine banked, we have the opportunity to explore and validate alternative and evolving IEBs as well as mechanisms. The systematic approach presented here may serve as a model for the evaluation of other chemopreventive agents for prostate cancer and other solid organ tumor types.

## Figures and Tables

**Figure 1 F1:**
[figure not shown]
Primary Mechanism of Green Tea Polyphenons (Polyphenon E) in Prostate Carcinogenesis.

**Figure 2 F2:**
[figure not shown]
Study Schema for a Phase II clinical trial of Polyphenon E in Prostate Cancer Chemoprevention targeting High-grade Prostatic Intraepithelial Neoplasia (HGPIN) and Atypical Small Acinar Proliferation (ASAP).

**Table 1 T1:** Clinical evaluations and procedures.

Evaluation/Procedure	Screening/Pre-Randomization	Run-in	Baseline/Random-ization	Months 1–11	Month 3	Month 6	Month 12 or Early Termination	Post-Tx Day 7 Phone Contact
Informed Consent Signed/Registration Number Assigned	▪							
Demographic Questionnaire	▪							
Physical Exam (weight, height and vital signs, hip circumference measurement)	▪						▪	
AEs (Signs and Symptoms)	▪	▪	▪	▪	▪	▪	▪	▪
Concomitant Medications	▪	▪	▪	▪	▪	▪	▪	▪
PSA	▪^1^				▪^3^	▪	▪	
DRE	▪^1^				▪^3^	▪	▪	
Serum Chemistry and Hematology (CMP, CBC)	▪				▪	▪	▪	
Hepatic Function Panel^2^, LDH, PT/PTT	▪			▪	▪	▪	▪	
Pathology – Biopsy (12 core biopsies)	▪^3^					▪^4^	▪	
Dispense Multivitamin/Mineral Supplement	▪		▪	▪	▪	▪		
Collect 2-day Diet Recall Forms^5^			▪		▪	▪	▪	
Compliance Check (review log and perform pill count)			▪	▪	▪	▪	▪	
Randomization			▪^6^					
Collect Serum for Banking			▪			▪	▪	
Request Biopsy Specimen for Endpoint Measurements and Banking			▪				▪	
Plasma Catechin Levels			▪			▪	▪	
Diagnostic Markers^7^			▪			▪	▪	
LUTS			▪		▪	▪	▪	
QOL^8^			▪		▪	▪	▪	
Dispense Study Agent			▪^9^	▪^9^	▪^9^	▪^9^		

1 DRE does not need to be performed at the screening/pre-randomization visit if results are available from TRUS performed prior to diagnostic biopsy and within six months of randomization.

2 Includes albumin, direct and total bilirubin, alkaline phosphatase, ALT, AST, total protein.

3 Results from the diagnostic biopsy will be used to confirm presence of HGPIN or ASAP for eligibility; if the subject is randomized, slides from the diagnostic biopsy will be obtained and used for pre-intervention histopathology drug effect measurements.

4 Men will be re-biopsied at six months (if enrolled with ASAP) or if PSA increases >0.75 ng/ml or development of a palpable prostate nodule is observed in men with HGPIN. Considering the normal day to day variance of PSA, any rise in PSA will be confirmed with a second test prior to repeat biopsy at 6 months (HGPIN). If biopsy is performed, samples for endpoint analysis and banking will be requested.

5 Dietary recall forms and instructions will be distributed at the screening and month 2, 5 and 11 clinic visit to be completed by the subject prior to the next scheduled visit.

6 Subjects should not be randomized until eligibility has been confirmed; if the subject does not meet eligibility criteria, he should be taken off study.

7 Prostate cancer-associated diagnostic marker-1 (PCADM-1) level in serum; HGPIN-specific marker ABCA5 in urine. Urine for ABCA5 should be collected as the first void urine at the site visit, prior to any manipulations (*e.g.*, DRE).

8 Rand Short-form (SF)-36 (Medical Outcomes Study SF36).

9 One bottle (100 capsules) of study drug will be dispensed after randomization. Additional bottles will be dispensed as needed at monthly clinic visits to ensure that the subject has enough study drug to last until the next clinic visit.

10 Please note that PSA is only required at month 3 for those men enrolled with ASAP.

11 Please note that DRE is only required at month 3 for those men enrolled with ASAP.
